### Criteria for discontinuing or modifying allocated interventions {11b}

#### Criteria for discontinuing

Participants withdraw the trial spontaneously.Pregnancy (pregnant participants should withdraw the trial).Adverse events that persuade investigators to urge participants to leave the trial as early as possible.Poor compliance of participants with the research program, and exercise adherence rate is not in the range of 80–120%.Occurrence of serious adverse reactions related to exercise intervention.In this study, major mistakes are detected in the clinical research program, making it difficult to evaluate the efficacy of the intervention. In addition, a significant deviation is observed in the implementation of a well-designed program.

### Strategies to improve adherence to interventions {11c}

To increase participants’ compliance in the test group, it will be essential to record details of exercise (including date, start/end time, and rate) and take screenshots to retain data by the mobile phone application. Participants’ details of exercise in the control group will be recorded according to their exercise habits. Data from both groups will be forwarded to research team every week. Weekly telephone follow-up will be performed to strengthen participants’ compliance and to provide a recommendation sticking to an exercise program.

### Relevant concomitant care permitted or prohibited during the trial {11d}

*This* trial will not impose *special requirements for* care and interventions.

### Provisions for post-trial care {30}

When the participants complete the trial, they will receive standardized treatment based on the guideline.

### Outcomes {12}

#### Primary outcome

Primary outcome will include the number of patients whose body fat is reduced after 12 weeks.

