**Methods:**

In this randomized, open-labeled, controlled trial, a total of 60 overweight and obese patients with gout [body mass index (BMI) ≥ 24 kg/m^2^; age,18–55 years old] are equally randomized (1:1) into two groups (*n* = 30): moderate-intensity aerobic exercise group (MIAEG), heart rate reserve (HRR) = [(HRmax-HRrest) × 60% intensity] + HRrest, and control group (CG). The moderate-intensity aerobic exercise training program will be conducted for 30–40 min/session and 3 days/week for 12 weeks. Participants in the CG will be asked to avoid making changes in their exercise habits. There will be no limitation in the type of exercise. The primary outcome is the number of patients whose body fat is reduced after 12 weeks. The secondary outcomes include the changes in BMI, waist-to-hip ratio (WHR), insulin resistance index (IRI), serum uric acid (sUA), serum creatinine (SCr), estimated glomerular filtration rate (eGFR), triglycerides (TG), total cholesterol (TC), low-density lipoprotein cholesterol (LDL-C), high-density lipoprotein cholesterol (HDL-C), hepatic steatosis, and adverse effects after 12 weeks. One-way analysis of variance (ANOVA) will be used to compare the mean values of normally distributed variables between MIAEG and GC.

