### Trial design {8}

This is a randomized, open-label, controlled trial over 12 weeks. A total of 60 patients with gout who meet the study criteria are randomized (1:1) to the moderate-intensity aerobic exercise group and control group (Fig. 1). The trial framework is exploratory.

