### Research procedures

Screening

According to the ACR/EULAR criteria and the scoring system for gout presented in 2015, we will adopt the following criteria: patients with gout (in intermittent or chronic phase; there will be no gout flare in the last 2 weeks); patients aging 18–55-years-old; patients with BMI ≥ 24 kg/m^2^.(2)Enrollment

Participants will be randomly assigned into test and control groups, and participants in both groups will be treated for 12 weeks.(3)Program

Moderate-intensity aerobic exercise group:

The target HR calculated by the HR reserve method will be used as the target HR in the moderate-intensity aerobic exercise. The exercise speed of patients with gout corresponding to the MET value of target HR calculated by the HR reserve method will be utilized as the main exercise program in the test group. The HR reserve will be calculated as follows: HRR = [(HRmax-HRrest) × 60% Intensity] + HRrest. The exercise will be performed for 30–40 min/session and 3 times/week. The total duration of exercise is 120–150 min/week.

Control group:

No restriction will be applied in terms of the mode of exercise, and participants can select their preferred exercise regimens during the trial. They will be asked to avoid making changes in their exercise habits.(4)Laboratory indicators

Weight, body fat, waist circumference, hipline, blood pressure, blood glucose, routine blood test, urine routine test, and renal and liver functions will be assessed. The body composition will be determined by BIA.(5)Follow-up

Follow-up will be conducted at baseline, 6 weeks ± 3 days, and 12 weeks ± 3 days.(6)Data and specimen collection

Participants’ demographic data will be collected in terms of age, gender, blood pressure, course of the gout, history of medications, etc. Participants will be followed up for three times (baseline, 6 weeks, and 12 weeks after the test) to measure height, weight, body fat, waist circumference, hipline, BMI, blood routine (e.g., sUA), urine routine (including urinary pH), and biochemical indices (blood glucose, serum insulin, triglycerides (TG), total cholesterol (TC), low-density lipoprotein cholesterol (LDL-C), high-density lipoprotein cholesterol (HDL-C), serum creatinine (SCr), and estimated glomerular filtration rate (eGFR)). Predictors of relevant systems will be evaluated after 12 weeks. Biological specimens will be destroyed after testing.

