### Sample size {14}

This is a differential test, and the primary outcome is the number of patients whose body fat is reduced after 12 weeks of exercise intervention. The sample size is 50 with involvement of 25 patients in the intervention and control groups. Considering a 15% dropout rate, the final sample size will be 30 patients per each group, and the two groups will totally include 60 cases.

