### Statistical methods

#### Statistical methods for primary and secondary outcomes {20a}

Statistical analysis will be carried out using SAS 9.4 statistical software, and all data will be expressed as mean ± standard deviation (SD) or percentage (%). Differences in demographic data, anthropometric measurement, blood biochemical parameters, and health-related physical fitness components between baseline and week 12 groups will be analyzed using the paired *t*-test. One-way analysis of variance (ANOVA) will be used to compare the mean values of normally distributed variables between MIAEG and GC. Statistical analysis was carried out using SPSS (version 26). A two-tailed significance level of 0.05 was used for all tests. *P* < 0.05 is considered statistically significant.

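### The primary outcome counts patients with any fall in body fat, with no minimum reduction; this costs precision and leaves the size of fat change unestimated by any listed outcome

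*Protocol article*

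**What the plan says.** The section on the primary outcome reads "Primary outcome will include the number of patients whose body fat is reduced after 12 weeks". The abstract agrees ("The primary outcome is the number of patients whose body fat is reduced after 12 weeks"), and so does Sample size {14} ("the primary outcome is the number of patients whose body fat is reduced after 12 weeks of exercise intervention"). None of the three gives a minimum reduction or a margin for measurement error.

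The underlying measurement is continuous. Under Research procedures, "The body composition will be determined by BIA", and body fat is recorded at baseline, 6 weeks and 12 weeks. The secondary outcomes list BMI, waist-to-hip ratio, lipids, insulin resistance, hepatic steatosis, uric acid, renal measures and adverse effects. Change in body fat is not among them. Objectives {7} asks for the effect of the exercise programme on body composition.

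On size: "The sample size is 50 with involvement of 25 patients in the intervention and control groups", and then "Considering a 15% dropout rate, the final sample size will be 30 patients per each group". No response rates, standardised difference, SD or power are stated. Statistical methods {20a} sets the error rate ("A two-tailed significance level of 0.05 was used for all tests") and names ANOVA of means for the comparison between arms. Logistic regression appears only under additional analyses {20b}.

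**The concern.** Bioimpedance readings vary between occasions. If success is a week-12 reading below baseline by whatever amount, a patient whose body fat has not truly changed is classified by measurement error, and a trivial fall scores the same as a large one. Cutting a continuous measurement at zero also discards information, which matters in a trial planned on 25 evaluable patients per arm whose own discussion concedes a small sample. Finally, the difference between two proportions of patients reduced does not say how much fat was lost, and no other listed outcome supplies that quantity.

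**Working it through.** **The plan's own figure.** 25 / (1 − 0.15) = 29.4, rounded up to 30 per arm and 60 in total, so the dropout step reproduces. The starting figure of 25 per arm cannot be checked, because no rates, effect or power are given.

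**Inputs.** From the protocol article: 25 evaluable or 30 randomised per arm, 1:1 allocation, two-sided 0.05. Assumed here: the change in body fat is normal with the same SD in both arms; *d* is the extra mean loss with exercise divided by that SD; mean control change is zero unless a drift is stated.

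**Step 1: chance that an unchanged patient counts as reduced.** With mean loss *m* in SD units of change, P(reduced) = Φ(*m*).
- *m* = 0: Φ(0) = 0.50. This does not depend on how large the bioimpedance error is, only on its being symmetric about zero.
- *m* = ±0.25: 0.40 to 0.60.
- *m* = ±0.5: 0.31 to 0.69.

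**Step 2: information kept by the split.** For a normal variable cut at the control median, asymptotic efficiency is φ(0)² / (0.5 × 0.5) = (1/2π) / 0.25 = 2/π = 0.64. On that scale 25 per arm works like 25 × 0.64 ≈ 16 per arm, and 30 like about 19.

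**Step 3: power over a range of effects.** Control proportion 0.50, exercise proportion Φ(*d*). Count: uncorrected chi-square, with binomial probabilities summed over all tables in which |z| exceeds 1.96. Continuous change: two-sample *t*-test, noncentral *t*.

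| *d* | Proportions reduced | 25/arm: count vs continuous | 30/arm: count vs continuous |
|---|---|---|---|
| 0.5 | 50% vs 69% | 31% vs 41% | 33% vs 48% |
| 0.8 | 50% vs 79% | 60% vs 79% | 65% vs 86% |
| 1.0 | 50% vs 84% | 77% vs 93% | 82% vs 97% |
| 1.2 | 50% vs 88% | 88% vs 99% | 92% vs >99% |

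The article names no test for the count. Chi-square is the favourable choice: at *d* = 0.8 and 25 per arm, Fisher's exact test has 47% power.

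**Step 4: what the count can detect.** At 25 per arm against 50% in controls, 85% reduced with exercise gives 79.0% power and 86% gives 81.8%. So 80% power needs about 50% vs 86%.

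**Step 5: sensitivity to drift.** At *d* = 0.8 and 25 per arm, letting the control mean drift from −0.5 to +0.5 SD moves chi-square power between 49% and 65%. The *t*-test stays at 79%, because a common drift leaves the difference in means unchanged.

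**The case against.** The strongest reply has several parts.

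- **A margin may exist elsewhere.** No sentence says that any fall above zero counts. The article says only that body fat is reduced, and the approved full protocol (V20220408) is not shown. This stands as a limit: the 50% figure belongs to the outcome as written. For the same reason, the absence of a choice between fat mass and percentage is detail an article may leave out, and is not a fault by itself.
- **Randomisation protects the comparison.** A reader might infer that the count cannot tell real fat loss from noise. That is true of an individual patient but not of the trial. Data collectors and endpoint adjudicators are to be blinded, noise affects both arms alike, and the control proportion is the reference. The cost is in precision, not validity.
- **A count does give an effect measure.** A reader might infer that no effect size would be available. A risk difference or odds ratio can be reported, and an odds ratio with 95% CI is planned under additional analyses. What is missing is the size of the change in fat. The planned *t*-tests and ANOVA could be applied to body fat, so the data are not thrown away, but nothing makes that comparison a listed outcome.
- **Half of controls need not be successes.** Controls receive education on exercise, alcohol and diet, so zero mean change is an assumption. Step 1 shows the range.
- **The power gap depends on an unknown effect.** At *d* = 0.5 both endpoints are badly underpowered; at *d* = 1.2 both exceed 80%. Only the direction is constant.
- **The trial is labelled exploratory.** That does not remove the point, since an exploratory trial has particular need of an estimated size of effect.

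**Conclusion.** The point holds as a loss of precision and a mismatch with the objective. As written, the primary outcome has no minimum reduction. A patient without true change counts as reduced about half the time if error is symmetric and there is no drift (31–69% for drifts up to ±0.5 SD). Splitting at the control median keeps about 64% of the information. The count has less power than the continuous change at every effect tried: by 10 to 19 percentage points at 25 per arm and, for *d* from 0.5 to 1.0, by 15 to 21 points at 30 per arm. These sizes assume normal changes, equal SDs and illustrative values of *d*, because the article states no effect size. The documents do not support saying that the randomised comparison is invalid, that no effect measure is possible, or that half of the control arm will be successes. The trial can run as written, but its main result would be less precise than its data allow and would not say how much body fat changed.

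**What to change.** Make week-12 body fat the primary outcome, as one named bioimpedance variable. Compare arms by ANCOVA adjusted for the baseline value, and report the mean difference with its 95% CI. Keep the number of patients with reduced body fat as a supportive secondary outcome. Restate the sample size justification for a difference in means, giving the assumed difference, SD and power.

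The cost is an ethics and registry amendment of the primary outcome, which is a substantial change in an open-label trial and must be made before any outcome data by arm are seen. No new measurement is needed, since body fat is already taken at all three visits. If the primary outcome can no longer be changed, naming the baseline-adjusted mean difference in body fat as a key secondary outcome, with its CI, would still supply the missing size of effect, but would leave the precision of the primary comparison as it is.

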#### Secondary outcomes

Secondary outcomes will include changes in BMI, waist-to-hip ratio (WHR), TG, TC, LDL-C, HDL-C, insulin resistance index (IRI), hepatic steatosis, sUA, SCr, eGFR, and adverse effects after 12 weeks. Adverse events will be monitored during the 12 weeks of study, including the rate of gout flare. Any adverse reactions that occur during the study will be recorded in the “Adverse Reaction Table,” and participants will be followed up until symptoms disappear or indicators return to normal. In the serious adverse events, necessary measures will be taken immediately to ensure participants’ safety.

### Participant timeline {13}

The participant timeline in shown in Fig. 2.

**Fig. 2 Fig2:**
[figure not shown]
SPIRIT figure of enrolment, interventions, and assessments

### Sample size {14}

This is a differential test, and the primary outcome is the number of patients whose body fat is reduced after 12 weeks of exercise intervention. The sample size is 50 with involvement of 25 patients in the intervention and control groups. Considering a 15% dropout rate, the final sample size will be 30 patients per each group, and the two groups will totally include 60 cases.

### Recruitment {15}

Participants will be recruited from Shenzhen Traditional Chinese Medicine Hospital, People’s Hospital of Longhua District Shenzhen, and the Second Affiliated Hospital of Guizhou University of Traditional Chinese Medicine between September 2022 and January 2024. A total of 60 adult patients with gout (no gout flares can be detected in the last 2 weeks) from outpatient and ward screening programs aging 18–55 years old will be invited to attend in the bioelectrical impedance analysis (BIA). Once a patient is confirmed to be eligible, a physician will review the study procedures and requirements with the patient and ask his/her commitment to the study and acceptance of randomization. Written informed consent will be obtained from each participant, and baseline evaluation will be performed, which will be immediately scheduled by the physician assistant.

### Assignment of interventions: allocation

#### Sequence generation {16a}

Statisticians will adopt the PROC PLAN process of the SAS 9.4 statistical software to generate a random list by blocked randomization of variable block lengths.

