## Methods: participants, interventions, and outcomes

### Study setting {9}

The present study will be completed at Shenzhen Traditional Chinese Medicine Hospital, People’s Hospital of Longhua District Shenzhen, and the Second Affiliated Hospital of Guizhou University of Traditional Chinese Medicine from May 16, 2022, to May 16, 2024. Written informed consent is obtained from all participants prior to the commencement of the study. All enrolled participants will be fully informed about the objective, methods, and possible risks of the study.

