#### Concealment mechanism {16b}

In the mechanism of implementing the allocation sequence, [name] generated the allocation sequence; sequentially numbered, opaque, sealed envelopes can be reproduced when needed.

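### One blocked list is described for three hospitals, with no centre stratum and no centre term in the stated analysis: a modest, cheaply avoidable loss of balance and precision

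*Protocol article*

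**What the plan says.** Study setting {9} and Recruitment {15} name the same three hospitals. Sample size {14} starts from 25 evaluable patients per arm and continues: "Considering a 15% dropout rate, the final sample size will be 30 patients per each group", so 60 are randomised 1:1. How the 60 divide between hospitals is not stated.

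Sequence generation {16a} says that statisticians will use SAS PROC PLAN to "generate a random list by blocked randomization of variable block lengths". Block lengths are not given. Neither this section nor the two that follow it mention centre.

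Concealment mechanism {16b} says that "sequentially numbered, opaque, sealed envelopes can be reproduced when needed". It does not say what is reproduced, by whom or under what control. Implementation {16c} separates the roles: a university statistician generates the sequence, doctors enrol, and a nurse assigns.

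Section {20a} compares arms by one-way ANOVA, with arm as the only factor mentioned. Section {20b} adds a logistic model whose covariates come from univariate screening, so centre is not a prespecified covariate there either.

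**The concern.** Permuted blocks balance the arms along the order in which a list is used. If consecutive entries go to whichever hospital enrols next, each block is scattered over three sites and the balance holds only for the trial as a whole. Centre then varies by chance between arms, and nothing in the stated analysis takes it out.

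Centre could plausibly relate to the primary outcome, the number of patients whose body fat falls by week 12. Patients and local conditions for exercise may differ between hospitals, and body composition is measured by bioelectrical impedance without a device common to the sites being named. With 30 patients per arm, avoidable noise is worth removing. At stake are balance within centres and some precision, not the validity of the randomisation.

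**Working it through.** **The plan's own figure.** 25 / (1 − 0.15) = 29.4, rounded up to 30 per arm, 60 in total. This reproduces. The 25 cannot be checked, because no response rates or power are given; the present point does not depend on it.

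**Inputs.** From the article: N = 60, 1:1, three centres, variable blocks. Assumed, because the article gives neither: centre sizes 20/20/20, 30/20/10 or 36/12/12, and block lengths drawn from {4, 6} or {2, 4, 6}.

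**Three ways to use the list**, simulated with at least 4,000 runs per scenario. Each cell gives the range over the six combinations of centre size and block set.

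| Use of the list | Mean largest within-centre arm difference | Some centre off by ≥ 4 | ≥ 6 | ≥ 8 |
|---|---|---|---|---|
| (a) One list, in enrolment order across sites | 4.0–4.4 | 63–69% | 29–37% | 9–14% |
| (b) One list, consecutive envelope runs per site | 1.0–1.2 | 3–5% | 0 | 0 |
| (c) Separate blocked list per centre | 0.9–1.1 | about 0 | 0 | 0 |

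Under (a) the overall arm difference still averages only 0.4–0.5 patients, so the trial-wide 1:1 ratio is safe.

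**Cross-check without blocks.** Draw a 20-patient centre at random from 30 + 30. The hypergeometric probability of 13:7 or worse (a difference of at least 6) is 2 × P(X ≤ 7) = 0.170. By simulation, at least one of three such centres reaches it in 0.356 of trials. With blocks, use (a) at 20/20/20 gives 0.35–0.37. Blocking a shared list therefore gives almost no protection within centres.

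**What this costs in precision.** Take three equal centres, an overall response of 50% and 30 per arm.

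- Unadjusted: SE = √(0.25 × 2/30) = 12.9 points.
- Centre rates 30/50/70% (assumed): mean within-centre variance = (0.21 + 0.25 + 0.21)/3 = 0.2233. With centres balanced and centre accounted for, SE = √(0.2233 × 2/30) = 12.2 points.
- Centre rates 20/50/80% (assumed, extreme): (0.16 + 0.25 + 0.16)/3 = 0.19, so SE = √(0.19 × 2/30) = 11.3 points.

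The share of variance due to centre is (0.25 − 0.2233)/0.25 = 11% in the first case and (0.25 − 0.19)/0.25 = 24% in the second. As a standard deviation of the arm difference, that is √(0.0267 × 2/30) = 4.2 points and √(0.06 × 2/30) = 6.3 points. These are part of the 12.9, not an addition to it. If centres do not differ in response, nothing is gained.

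**The case against.** The strongest reply is that the lack of a stratum is read from silence. The article condenses a fuller protocol; it does not say that the list is unstratified, or that it is shared in order of enrolment. Paper envelopes at three hospitals may well have been divided among them, and consecutive runs would leave little imbalance. This stands, and it makes the 63–69% conditional on use (a). What remains is that the article does describe a list in the singular, names its software, procedure and block scheme, and specifies no centre term.

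It is also fair to say that unstratified randomisation is a legitimate choice in a trial that calls itself exploratory, and that lists per centre make guessing easier at a small open-label site. Both stand. They make this a design improvement rather than a correction of an error.

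A reader might infer two stronger things. The first is that centre imbalance biases the result. It does not: under valid randomisation the chance imbalance averages to zero, and the ordinary unadjusted standard error already contains it. A constant offset between impedance devices would also largely cancel, since the outcome is a change within each patient.

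The second is that reproducible envelopes let an allocation be seen before enrolment. The article does not support that. Numbered, opaque, sealed envelopes, variable blocks and separated roles are a standard arrangement, and the phrase may mean only that the sequence can be regenerated from its program. Nothing says that site staff may make, hold or open duplicates.

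**Conclusion.** The point holds as a modest one. The article describes one variable-block list for three hospitals, with centre in neither the randomisation nor the stated analysis. If the list runs in enrolment order across sites, some centre will be off by 4 or more patients in about 63–69% of trials, against about 3–5% with consecutive runs per site and about 0 with a list per centre. These figures rest on assumed centre sizes and block lengths.

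The price is precision: roughly 12.9 against 12.2 points of standard error at assumed centre rates of 30/50/70%, and 11.3 in the extreme case. The treatment comparison remains unbiased, overall balance is protected, and no weakness in concealment is demonstrated. The wording about reproducing envelopes deserves a clarification and no more.

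**What to change.** Run the same PROC PLAN code once per hospital, giving three variable-block lists, each with its own numbered envelope series. Say so in {16a} and {16b}. Include centre as a prespecified term in the primary between-arm comparison; for the difference in proportions, a Mantel–Haenszel estimate stratified by centre would do. If recruitment has begun ({15} puts its start at September 2022), leave the list alone and add only the centre term, before any outcome data are seen by arm.

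The cost is a few lines of code, a few sentences, two degrees of freedom and no extra patients. The drawback is slightly easier guessing at a very small centre, which the variable blocks limit.

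As a minor clarification, reword {16b} to say that the statistician can regenerate the sequence from the archived program and seed, and that issued envelopes are not duplicated.
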